#### Secondary outcomes

Secondary outcomes are listed in Table 2. They focus primarily on behavior changes and skill acquisition related to specific aspects of the intervention program. Because of its potential relevance to many of the memory support strategies taught in the intervention, a prospective memory test was added to the cognitive outcomes.

**Table 2 Tab2:** Secondary outcome measures

*Secondary Outcomes*	*Specific Measures*
Self-efficacy	Coping Self efficacy (CSES) [56]
Mood and Well-being	Center for Epidemiologic Studies Depression Scale (CES-D) [57] Perceived Stress Scale (PSS) [58] Life Satisfaction [59, 60] Purpose in Life [61] Brief Resiliency Scale [62]
Physical Performance	The Short Physical Performance Battery (SPPB) [63]
Self-rated Health and Quality of Life (QoL)	Patient Reported Outcomes Measurement Information System (PROMIS) General health Quality of Life (QoL) [64]
Instrumental Activities of Daily Life (IADL) Disability	Cooperative Study ADL Prevention Instrument* (ADCS-ADL-PI) [65]
Compensation Strategy Use	Everyday Compensation (EComp)* [66, 67]
Health Behaviors Directly Targeted in the Intervention	Community Healthy Activities Model Program for Seniors (CHAMPS) [68] Positive Affect and Negative Affect Scale (PANAS) [69] Gratitude Questionnaire [70] Mindfulness Questionnaire [71]

^*^ These questionnaires will also be completed by a study partner to collect additional information about how the participant is functioning in their daily life if possible (not required)

### Predictors of treatment response

In accordance with previous intervention research recommendations [72], person-specific characteristics of treatment response are examined. In addition to demographic factors, potential predictors include questionnaires assessing indicators of self-determination (autonomy, competence, and relatedness) and health literacy. The SDT construct of autonomy and self-regulation of health behaviors is measured using the Treatment Self-Regulation Questionnaire (TSRQ) (adapted) [73]. The construct of competence is measured by the Perceived Competence for Healthy Brain Aging (adapted) [74], and the construct of relatedness and self-perceived social support by the Social Support for Health Behaviors (adapted) [75]. Health literacy and the perceived ability to manage one’s health is measured using the Patient Activation Measure (PAM-13) [76]. The following demographic characteristics are also collected: age, sex, level of education, ethnicity, and socioeconomic status (using a 9-point scale from 1 [$0 – $9,999] to 9 [$80,000 and more]).

### Qualitative interviews

Mixed methods research [77] is a valuable way to examine complex health interventions that are built on multiple components that may act both independently and interdependently [78]. To expand understanding of how to deliver a preventative compensation and lifestyle intervention to individuals with SCD, a subset of participants in the structured intervention condition will be asked to complete a qualitative semi-structured interview in which they answer open-ended questions about their experience in the intervention. The goal of the qualitative interviews is to identify barriers and facilitators to uptake of and adherence to the components of the intervention, as well as to elicit feedback that could lead to improvements in the intervention (e.g., components the participants found helpful or unhelpful). This information will complement the quantitative analyses and provide further insight on the relationship between adherence and the primary and secondary outcome measures, components of the intervention important for treatment effectiveness, and reasons for poor uptake. The qualitative interview will be recorded, transcribed, and coded using standard qualitative research methods. We aim to collect this information after completion of the 6-month intervention, as well as at other follow up time points across participants with high and low adherence rates derived from EMMA usage metrics.

### Data and safety monitoring

This study will be monitored by an external Safety Officer (SO), which will act in an advisory capacity to the National Institute on Aging (NIA) and the primary investigators (PIs) to monitor participant safety, data quality, and the progress of the study. The SO will meet with the contact PI ([name]) on a quarterly basis and will complete a safety monitoring report to the NIA twice yearly.

We expect adverse events (AEs) associated with this intervention to be minimal and consistent with risks associated with normal daily activities and an active lifestyle (e.g., muscle soreness from physical activity). AEs will be tracked in the study database. We will employ multiple approaches to ensure complete and accurate collection of information about AEs. All participants will be prompted to report AEs and serious adverse events (SAEs) at their outcome assessment visits (approximately 6, 12, and 18 months). Participants may also spontaneously report AEs/SAEs during their intervention meetings. All AEs/SAEs will be reviewed within 24 hours by the study clinician/medical monitor to determine seriousness, whether the event was unexpected and related to the intervention. AEs that are serious, unexpected, and related to the intervention will be reported immediately to the project PIs and to the Institutional Review Board (IRB), SO, and NIA.

### Sample size and power calculations

The goal is to enroll 225 individuals into this trial, anticipating 20% drop-out. The trial was powered to detect intervention effectiveness (Aim 1). Assuming 180 participants complete the entire study with a correlation between repeat assessments of at least 0.4, alpha = 0.05 and a two-sided test, we will have over 80% power to detect a difference in slopes between baseline and immediately post-intervention as small as 0.5 standard deviations (SD). If alpha is reduced to 0.025 to account for the two primary outcomes, the minimum detectable difference in slopes is 0.54 SD. Our preliminary studies had a difference in slopes of 0.5–0.6 SD, although we expect the outcomes proposed for this study to be more sensitive to change in behaviors than those used in our preliminary studies.

### Planned statistical analysis

#### Intervention effectiveness

To evaluate the success of randomization, we will first compare between interventions (structured, self-guided) on demographics and other variables using two-sample t-tests (continuous) and chi-square tests (categorical); Wilcoxon rank sum tests or Fisher’s exact tests will be used instead if assumptions are violated. If differences between intervention groups exist, follow-up analyses will include those variables as covariates to ensure any observed intervention effect is not due to other differences between the groups. Primary analyses will be intent-to-treat analyses, that estimate intervention effects based on groups as randomized. Due to the repeat assessments over time across individuals (baseline, immediately after the 6-month intervention, and at 6- and 12-months post-intervention), repeated measures, random effects models will be used to estimate differences in rate of change between the groups at different time points. The main intervention effect will be defined as the difference between groups from baseline to immediately after the 6-month intervention, although later time points will assess maintenance of those effects. These models will incorporate random intercepts and slopes to account for between-person variation in overall level and change over time. All model assumptions will be checked and transformations or repeated measures approaches for non-normal data, such as generalized estimating equation (GEE) approaches will be used if needed. List-wise deletion will be used if < 5% of the data are missing; multiple imputation will be used if > 5% of the data are missing. If data appear to be missing not at random or exceeds > 20% missingness (which we have put procedures in place to prevent), we will conduct sensitivity analyses using Wu-Carrol and Diggle-Kennward approaches that our team has previously applied in RCT trials [79, 80]. Similar analyses will be completed with the secondary outcome measures.

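### The only stated covariate rule selects covariates by baseline significance tests between randomised arms, so the adjusted analysis depends on chance and is not fixed in advance

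*Protocol article*

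**What the plan says.** The rule is in the protocol article under Planned statistical analysis, Intervention effectiveness. As a check on randomisation, the arms are first compared on demographics and an unspecified set of other variables. The tests are t-tests and chi-square tests, with rank-sum or exact tests as fallbacks. Then: "If differences between intervention groups exist, follow-up analyses will include those variables as covariates". The stated purpose is "to ensure any observed intervention effect is not due to other differences between the groups". No significance level or size of difference is given.

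The primary analysis is described separately: "Primary analyses will be intent-to-treat analyses, that estimate intervention effects based on groups as randomized". The method is that "repeated measures, random effects models will be used to estimate differences in rate of change between the groups at different time points", and the contrast is fixed: "The main intervention effect will be defined as the difference between groups from baseline to immediately after the 6-month intervention". No covariate is named for this model and none is ruled out. The baseline value of the outcome is one of the repeated measures. The secondary outcomes are to be analysed in a similar way.

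The section on predictors of treatment response lists the demographics available: "age, sex, level of education, ethnicity, and socioeconomic status". The Randomization section describes 2:1 allocation in blocks of 3 or 6 and mentions no stratification factor.

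**The concern.** With properly generated allocation, the null hypothesis of a baseline test between arms is known to be true. The test cannot show whether randomisation succeeded, and its p-value says nothing about whether the variable predicts cognition or everyday function. A strongly prognostic variable with a moderate imbalance can go unadjusted while an irrelevant one is added.

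Because the variable list is open and the threshold unstated, the adjusted model is known only after the data have been seen. The text also does not say what standing the adjusted result has if it differs from the unadjusted one. At stake are the reliability of the planned check against imbalance and the precision that pre-set covariates might bring.

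**Working it through.** **1. The plan's own power figure.** Inputs from Sample size and power calculations: 180 completers, correlation 0.4, two-sided alpha 0.05, difference 0.5 SD. The 2:1 allocation gives 120 and 60.
- SD of change = sqrt(2 × (1 − 0.4)) = 1.095.
- SE = 1.095 × sqrt(1/60 + 1/120) = 0.173.
- Power = Φ(0.5/0.173 − 1.96) = 82.3% (81.9% by noncentral t). The plan says over 80%.
- Minimum detectable difference at alpha 0.025 = (2.241 + 0.842) × 0.173 = 0.534 (0.538 by t). The plan says 0.54.

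Both figures reproduce with an unadjusted change score, so the stated power does not rely on covariates.

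**2. How often chance selects a covariate.** The threshold is not stated; 0.05 and independent tests are assumed.
- 5 variables (the number of demographics listed): 1 − 0.95^5 = 22.6%.
- 10 variables: 1 − 0.95^10 = 40.1%.
- 20 variables: 1 − 0.95^20 = 64.2%.
- At a threshold of 0.10 instead: 1 − 0.90^5 = 41% and 1 − 0.90^10 = 65%.

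The chance that any one variable is selected equals the threshold, whatever its prognostic strength.

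**3. Whether the rule protects against imbalance.** At full enrolment, 225 at 2:1 gives 150 and 75.
- SE of a standardised baseline difference = sqrt(1/150 + 1/75) = 0.141.
- A difference is flagged only beyond 1.96 × 0.141 = 0.28 SD.
- Chance of a difference above 0.2 SD: about 16% per variable, and about 57% for at least one of five.
- Of that 16%, about 5 points are flagged, so roughly 11 of every 16 such imbalances go unadjusted.
- Take an unflagged imbalance of 0.25 SD in a covariate explaining a share R² of the variance in change (assumed). It moves the estimate by sqrt(1.2 × R²) × 0.25, which is 0.09 SD at R² = 0.10 and 0.12 SD at R² = 0.20, against a target of 0.5 SD.

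**4. Simulation.** Settings: 10,000 trials each, 120 and 60 participants, six independent baseline variables of which one is prognostic, threshold 0.05, change score as outcome. Power is for 0.5 SD at alpha 0.05.

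| R² (assumed) | No adjustment | Test-based selection | Pre-specified |
|---|---|---|---|
| 0.10 | 82.6% | 82.7% | 86.0% |
| 0.20 | 81.9% | 82.3% | 89.2% |
| 0.30 | 82.6% | 83.7% | 93.1% |

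The prognostic variable was selected in about 5% of trials. Type I error under test-based selection was 4.3% to 4.8%.

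**5. Analytic check of the gain.** Replacing 1.2 by 1.2 × (1 − R²) in step 1 gives power of 86.1% at R² = 0.10 and 89.8% at R² = 0.20. At alpha 0.025 the unadjusted figure is 74.1%, rising to 78.9% and 83.8%.

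**6. When the gain applies.** The contrast is a change from baseline. A time-constant covariate entered only as a main effect adds the same amount at both visits and cancels from the change. A separate simulation used 150 and 75 participants, two visits, a random-intercept model, and a covariate explaining 30% of the variance at each visit. Adding the main effect gave an SE ratio of 1.000 with complete data and 0.991 with 20% random dropout. The gains in steps 4 and 5 therefore require covariate-by-time terms.

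**The case against.** The strongest reply is that the selected covariates are assigned to follow-up analyses, while a separate sentence labels the primary analysis as intention-to-treat on the arms as randomised. On the natural reading, the chance-selected model is a robustness check and does not decide the trial. In simulation the rule neither inflates type I error nor costs power against no adjustment, and the planned power holds without covariates. All of this stands, and it limits the point.

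A reader might infer that known prognostic variables are left out of the primary model. The article does not support that. It names no covariates for that model but excludes none, and a list may sit in the full protocol or SAP, which are not shown. The baseline outcome is in the model already.

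A reader might also expect a gain in precision from simply adding age, sex and education. That does not follow either: as main effects they largely cancel from the contrast, and the article gives no figure for how much of the variance in change they explain.

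The objection does not rescue the rule itself. The rule is stated in the article, not left to another document, and a robustness check whose content is drawn by chance does not do what is claimed for it.

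**Conclusion.** The point holds in limited form. The stated method for choosing covariates is unsound: it is driven by chance, open in its list and threshold, and blind to prognosis. The adjusted analysis is consequently not fixed in advance and gives little of the protection against imbalance that is its stated purpose. Compared with pre-specified adjustment, the simulated loss of power at R² of 0.10 to 0.20 is about 3 to 7 percentage points (86.0 − 82.7 and 89.2 − 82.3).

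The flagging rates rest on an assumed 0.05 threshold and independent tests. The power figures rest on an assumed R² for change and on covariate-by-time terms. The validity of the primary test is not in question.

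**What to change.** - Describe baseline characteristics by arm and drop the significance tests.
- Replace the selection rule with covariates pre-specified on prognostic grounds and already collected, for example age, sex and education, the same for both primary outcomes.
- Enter them with covariate-by-time terms so that they can act on the baseline-to-6-month contrast. The analyses of treatment responders already plan interactions of characteristics with assessment.
- Do not add the baseline outcome as a further covariate, since it is already one of the repeated measures.
- State which model is primary, adjusted or unadjusted, and report the other as a sensitivity analysis.

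The cost is wording, to be settled before unblinded data are seen, and a few degrees of freedom. With three covariates of one degree of freedom each, this means 3 main effects plus 3 interactions if time is a single term (6 in all), or plus 3 × 3 = 9 if the four visits are categorical (12 in all). That is small against 180 completers. If the covariates explain little of the variance in change, the gain in precision will be small, but the analysis will still be fixed in advance.

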### Randomization

After completion of baseline data collection, participants are randomly assigned using a block randomization strategy. Twice as many participants will be randomized into the target intervention to allow us to power Aim 3 (primarily within group analysis). Block sizes of 3 or 6 will be randomly chosen and assignments balanced within each block to ensure balance over time. Randomization is revealed to participants by a nonblinded study coordinator.

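### The primary effect is a change-from-baseline contrast with no stated conditioning on baseline; conditioning would cut its variance by 30% at the plan's floor correlation of 0.4

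*Protocol article*

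**What the plan says.** Under Intervention effectiveness, the protocol article plans repeated-measures models with random intercepts and slopes to "estimate differences in rate of change between the groups at different time points". Baseline is listed as one of the four repeated assessments, so it enters as an outcome. The primary contrast is then fixed: "The main intervention effect will be defined as the difference between groups from baseline to immediately after the 6-month intervention". The later visits serve to assess maintenance.

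The only covariate rule is conditional. Variables on which the arms are found to differ enter follow-up analyses. The section does not say that the baseline value of the outcome is a covariate in the primary model, nor that the arms share one baseline mean.

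Under Sample size and power calculations, the same contrast is powered as a "difference in slopes between baseline and immediately post-intervention as small as 0.5 standard deviations (SD"), "with a correlation between repeat assessments of at least 0.4". At alpha 0.025, for two primary outcomes, the stated detectable difference is 0.54 SD. The section also reports preliminary differences of 0.5 to 0.6 SD.

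Under Randomization, assignment follows the collection of baseline data.

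**The concern.** Because baseline is measured before assignment, the two arms have the same true baseline mean by design. A model that lets each arm have its own baseline mean ignores this. Its baseline-to-6-month contrast is then the simple difference in mean change, which carries the full noise of the baseline measurement. At a correlation below 0.5, that contrast is even noisier than a comparison of the 6-month values alone.

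What is at stake is precision. At the two-outcome alpha, the stated detectable difference of 0.54 SD lies inside the range of preliminary effects, so an effect at the lower end of that range would have less than 80% power. Baseline values that are already collected could remove that shortfall.

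**Working it through.** **Inputs**
- Enrolment: "The goal is to enroll 225 individuals into this trial, anticipating 20% drop-out"; 225 × 0.8 = 180, which agrees with "Assuming 180 participants complete the entire study".
- Allocation: "Twice as many participants will be randomized into the target intervention", so 120 and 60 completers if drop-out is equal in the two arms (assumption).
- Correlation ρ = 0.4, the plan's lower limit.
- Test: "alpha = 0.05 and a two-sided test"; also alpha 0.025.
- Outcome SD set to 1 at every visit (assumption; the article gives no SDs by visit).

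**Variance per unit of (1/n1 + 1/n2)**
- Change score: 2(1 − ρ) = 2 × 0.6 = 1.20
- 6-month value only: 1.00
- Conditional on baseline: 1 − ρ² = 1 − 0.16 = 0.84

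With 1/120 + 1/60 = 0.025:
- SE, change score: √(1.20 × 0.025) = √0.030 = 0.1732
- SE, conditional on baseline: √(0.84 × 0.025) = √0.021 = 0.1449

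**Reproducing the plan's figures.** With the change-score SE, power for 0.5 SD at alpha 0.05 is 81.9% (noncentral t; 82.3% by the normal approximation), which agrees with the claim of over 80%. The detectable difference at alpha 0.025 and 80% power is (2.241 + 0.842) × 0.1732 = 0.534 by the normal approximation and 0.538 by noncentral t, which rounds to the stated 0.54.

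Other variants at ρ = 0.4 and alpha 0.025 (noncentral t) do not give 0.54:

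| Variant | Detectable difference (SD) |
|---|---|
| Change score, 2:1 | 0.538 |
| Change score, 1:1 | 0.507 |
| 6-month value only, 2:1 | 0.491 |
| Conditional on baseline, 2:1 | 0.450 |

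Of these, only the unadjusted change score at 2:1 matches.

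**Effect of conditioning on baseline (ρ = 0.4, 120:60, noncentral t)**

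| Quantity | Change score | Conditional on baseline |
|---|---|---|
| Variance factor | 1.20 | 0.84 |
| Detectable difference, alpha 0.05 | 0.49 SD | 0.41 SD |
| Detectable difference, alpha 0.025 | 0.54 SD | 0.45 SD |
| Power for 0.5 SD, alpha 0.05 | 81.9% | 92.9% |
| Power for 0.5 SD, alpha 0.025 | 73% | 88% |

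**Check in the repeated-measures setting.** Generalised least squares with four visits, complete data and a common correlation of 0.4 gives a variance of 0.030 for the 6-month contrast when baseline means are free by arm, and 0.021 when they are constrained equal. The ratio is 0.70, as above. A repeated-measures model therefore does not recover the gain by itself; the common baseline mean or the covariate does.

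**Dependence on the correlation.** The ratio is (1 − ρ²) / [2(1 − ρ)] = (1 + ρ)/2:

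| ρ | 0.4 | 0.5 | 0.6 | 0.7 | 0.8 | 0.9 |
|---|---|---|---|---|---|---|
| Variance saved | 30% | 25% | 20% | 15% | 10% | 5% |

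**The case against.** **The model may already be efficient.** A repeated-measures model with baseline as an outcome equals the change score only if baseline means are free by arm. The article does not say which applies, and a power calculation does not dictate the model. This stands in part: that the analysis is unadjusted is inferred from the effect definition and the matching figures, and an analysis plan that is not shown could specify a common baseline. But the text and its numbers point the same way, and nothing in the article departs from them.

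**The size is one scenario.** This stands. The plan says at least 0.4, so under equal variances 30% is the largest gain. With unequal variances the ratio moves. As an illustration at ρ = 0.4, with assumed SDs, a 6-month SD of 1.2 times baseline gives 1.2096/1.48 = 0.82, and 0.9 times baseline gives 0.6804/1.09 = 0.62.

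**There is no validity problem.** This stands. A reader might infer that chance baseline imbalance biases the result. Under randomisation the change contrast is unbiased and keeps its type I error rate; the imbalance is the same loss of precision seen from another side.

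**Linear time.** From the talk of slopes and rates of change, a reader might infer that one linear slope over 18 months will be fitted and will miss the 6-month effect. The text does not support this. It estimates differences at different time points, fixes the main effect at 6 months and uses later visits for maintenance. The power section confines its slope to the interval from baseline to the end of the intervention. Random slopes describe variation between persons and do not make the fixed time effect linear.

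**Conclusion.** The point holds as avoidable loss of precision. The documents do not show bias, and the stated power is correct for the contrast that it describes. Under equal variances, conditioning on baseline cuts the variance of the primary effect by 30% at correlation 0.4, and by less at higher correlations. At 0.4 this brings the detectable difference at alpha 0.025 to 0.45 SD, below the whole 0.5 to 0.6 SD range of the preliminary studies.

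The result rests on four assumptions: 120:60 completers, equal SDs at baseline and 6 months, complete data, and arm-specific baseline means in the planned model. A reader might take the 30% as a fixed loss; it belongs to the plan's lowest correlation only.

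**What to change.** Under Intervention effectiveness, state that the primary model conditions on the baseline value of the outcome. There are two ways:
- put baseline in as a covariate for the post-baseline visits; or
- keep baseline as an outcome and give both arms a common baseline mean.

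Name one, since the two can differ when baseline or follow-up values are missing. Enter visit as a categorical factor, take the 6-month between-arm contrast as primary, and use the 12- and 18-month contrasts for maintenance. This does not require a particular covariance structure.

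Under Sample size and power calculations, restate the detectable difference on that basis: 0.41 SD at alpha 0.05 and 0.45 SD at alpha 0.025, for correlation 0.4 and 120:60 completers. If the analysis plan already conditions on baseline, bring both sections into line with it.

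The cost is wording only. Baseline values are already collected, and the sample size need not change.

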### Interventions

#### Overview

As noted above, participants take part in one of two possible intervention arms: the structured or self-guided intervention group. The self-guided education-only intervention was chosen as a comparison group to account for the impact of two general factors: 1) the provision of similar health information, and 2) the social support and stimulation provided by attending a group-based intervention. Each intervention group is matched in terms of the number and length of group sessions and exposure to other group participants and the interventionists. Both interventions are administered in a group format and consist of a total of 15 two-hour classes. The first 10 classes occur weekly, then the classes transition to bimonthly for one month and then monthly for the last three months. This format was chosen to facilitate mastery and gradually evolving autonomy and self-direction. The target size of each class is about 15 people to balance optimal group discussions with individualized attention. All intervention sessions will be digitally recorded. Recordings will be emailed to participants if they miss a session and make-up sessions are provided where needed.

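### Both arms are taught in classes of about 15, but the stated primary model and the power figure treat participants as independent; any positive within-class correlation inflates type I error and lowers the power of a valid analysis

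*Protocol article*

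**What the plan says.** Randomisation is at the level of the person (protocol article, Randomization): "After completion of baseline data collection, participants are randomly assigned using a block randomization strategy". Allocation is 2:1: "Twice as many participants will be randomized into the target intervention to allow us to power Aim 3 (primarily within group analysis").

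Treatment is then given in groups (Interventions, Overview): "Both interventions are administered in a group format and consist of a total of 15 two-hour classes". On class size: "The target size of each class is about 15 people to balance optimal group discussions with individualized attention". The same section gives the social support and stimulation of a group as one reason for choosing a class-based comparator, and the Study objectives list group support among the foundations of the structured arm.

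The primary model (Planned statistical analysis, Intervention effectiveness) is a repeated-measures random-effects model. The dependence it is introduced to handle is repeat assessment of the same person, and its random effects are described so: "These models will incorporate random intercepts and slopes to account for between-person variation in overall level and change over time". Generalised estimating equations appear only as a fallback for non-normal data. Class and interventionist are not mentioned in the analysis.

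The sample size section says "The goal is to enroll 225 individuals into this trial, anticipating 20% drop-out", and then "Assuming 180 participants complete the entire study with a correlation between repeat assessments of at least 0.4, alpha = 0.05 and a two-sided test", there is over 80% power for a difference of 0.5 SD from baseline to immediately after the intervention. At alpha 0.025 the minimum detectable difference is given as 0.54 SD. No ICC or design effect is stated.

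**The concern.** This is an individually randomised group-treatment design. At baseline participants are independent, because classes have not begun. By six months, members of a class have shared 15 sessions, the same discussions and the same stretch of calendar time, so their changes may be correlated. Matching the arms on group exposure balances the average effect of being in a group. It does not remove variation between classes, and that variation belongs in the standard error of the treatment contrast.

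A model with person-level intercepts and slopes cannot absorb such variation. If it exists, the standard error of the primary contrast is too small and an ineffective programme would be declared effective too often. An analysis that does allow for it has less power than the sample size section states. With only about 15 classes, about 5 of them in the control arm, few degrees of freedom remain for estimating class-level variance.

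**Working it through.** **Inputs from the protocol article.** 225 enrolled, 20% drop-out, 180 completers, 2:1 allocation, repeat-assessment correlation 0.4 (the stated minimum), two-sided alpha 0.05, difference 0.5 SD, class size about 15.

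**Derived.** Completers 120 and 60; enrolled 150 and 75. Classes: 150/15 = 10 structured and 75/15 = 5 self-guided. Completers per class: 15 × 0.8 = 12.

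**Assumed.** An ICC of six-month change between 0 and 0.10. The document gives no value.

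**1. Reproduce the stated figures**
- SD of change = √(2 × (1 − 0.4)) = 1.095.
- SE = 1.095 × √(1/120 + 1/60) = 0.173.
- Power = Φ(0.5/0.1732 − 1.96) = 82.3% (81.9% by noncentral t). Stated: over 80%.
- At alpha 0.025 the minimum detectable difference is 0.534 SD, and power at 0.54 SD is 80.4% by noncentral t. Stated: 0.54 SD.
- 180/0.8 = 225, as stated.

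All three figures are recovered with a design effect of exactly 1, so the calculation contains no allowance for classes.

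**2. Add the classes**
- Design effect DE = 1 + (12 − 1) × ICC.
- Actual size of the planned test at nominal 5% = 2 × (1 − Φ(1.96/√DE)).
- Power of a valid analysis for 0.5 SD = Φ(0.5/(0.1732 × √DE) − 1.96), or from a noncentral t with 10 + 5 − 2 = 13 degrees of freedom.

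| ICC | DE | Actual size of planned test | Valid power, normal | Valid power, 13 df | Detectable difference, normal / 13 df (SD) |
|---|---|---|---|---|---|
| 0 | 1.00 | 5.0% | 82.3% | 76.1% | 0.485 / 0.525 |
| 0.01 | 1.11 | 6.3% | 78.2% | 71.7% | 0.51 / 0.55 |
| 0.02 | 1.22 | 7.6% | 74.3% | 67.6% | 0.54 / 0.58 |
| 0.05 | 1.55 | 11.5% | 64.0% | 57.4% | 0.60 / 0.65 |
| 0.10 | 2.10 | 17.6% | 51.3% | 45.4% | 0.70 / 0.76 |

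A simulation of 10 against 5 classes of 12 (20,000 runs) agrees. The unadjusted test had size 5.0%, 6.3%, 7.6%, 11.9% and 17.6% down the rows. A class-level t-test held about 5%, with power 75.6%, 71.5%, 67.8%, 57.1% and 46.0%.

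**3. How much slack is there?** Power by normal approximation stays at 80% while DE ≤ (0.5/(0.1732 × 2.802))² = 1.062. The limiting ICC is 0.062/11 = 0.0056 with 12 per class, or 0.062/14 = 0.0044 with 15.

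**4. Sensitivity to the repeat-assessment correlation.** At 0.6, SD of change = √(2 × 0.4) = 0.894 and SE = 0.141. Valid power at ICC 0.02, 0.05 and 0.10 is then 89%, 81% and 68% (normal), or 84%, 75% and 62% (13 df). The size column does not change, because for a given ICC of change it depends only on DE.

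**The case against.** **The consequence is conditional.** A reader might infer that the trial's type I error does exceed 5% and that the stated power is not delivered. The document does not support that. Both need a positive ICC of change and none is given; at ICC 0 the size is 5% and power 82%. This stands, and the point is worded accordingly.

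**The correlation is held at its floor.** The plan says at least 0.4. At 0.6 a valid analysis keeps more than 80% power at ICC 0.02. This stands for power, but it does nothing for the inflated size.

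**The lower power figures belong to another test.** It is tempting to set 45% beside the stated power of over 80% as a defect of the planned test. The planned test would still reject about 76% of the time at ICC 0.05 when the true difference is 0.5 SD, though with inflated size. Inflated size (planned test) and lower power (corrected test) are alternatives and should not be added together. Likewise, the 76% at ICC 0 reflects the 13 degrees of freedom of a class-level test and is no error in the stated calculation.

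**The top of the ICC range may be generous.** Class effects enter only after baseline. Change variance is 1.2 times the single-visit variance, so an ICC of 0.10 on change means about 0.12 on the six-month score. Nothing in the document supports a value that high, but nothing excludes it. The inflation at 0.02 does not depend on it.

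**The class structure is partly inferred.** The counts of 10 and 5 are derived, fixed class membership is not stated, and make-up sessions and recordings may dilute clustering. They would not abolish it. The 180 are completers of the whole study, so numbers at six months may be higher.

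**A statistical analysis plan might add a class term.** It might. But the article does more than leave the matter open: it states the random-effects structure and gives a power figure that holds only under independence.

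**Conclusion.** The point holds in conditional form. The stated model and power calculation both ignore the class structure that the design creates in both arms. If six-month change correlates within a class, the planned test is too liberal: about 7.6% at ICC 0.02, rising to 17.6% at 0.10, against a nominal 5%. At the planning correlation of 0.4 the margin over 80% is nearly nil, and a valid analysis drops below it from an ICC of about 0.006. At ICC 0.05 the detectable difference is 0.60 to 0.65 SD, at or above the top of the 0.5–0.6 SD seen in the preliminary studies.

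These sizes rest on 12 completers per class, about 10 against 5 classes, equal class sizes and an assumed ICC. A higher repeat-assessment correlation eases the power loss only. Because the error runs towards a false positive on the primary efficacy claim, it should be settled before any unblinded analysis.

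**What to change.** - Record the class to which each participant belongs.
- In the primary model, prespecify a class random effect on the post-baseline visits, in both arms (baseline precedes the classes). Use Satterthwaite or Kenward-Roger degrees of freedom. Cluster-robust inference by class with a small-sample correction is an acceptable alternative. Keep the term whatever its estimate.
- Replace the single power sentence with a short table of power and detectable difference over ICC 0 to 0.10 and repeat-assessment correlations of 0.4 and above, saying that the ICC is assumed.

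The cost is one extra variance term, one more recorded variable and a rewritten power paragraph, with no extra enrolment. The downside is a stated detectable difference less favourable than 0.5 SD at the planning correlation, and some loss of power even if the ICC proves to be zero, because the class-level degrees of freedom are few.
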